## Abstract

**Introduction:**

Ovarian hyperstimulation syndrome (OHSS) is the most significant short-term complication of pharmacological ovarian stimulation. Symptoms range from mild abdominal discomfort to rare complications such as renal failure, thromboembolism and respiratory distress syndrome.

Currently, clinical practice typically involves monitoring the patient until the condition becomes severe, at which point they are admitted to hospital, where drainage of ascitic fluid (paracentesis) may take place. Preliminary studies have indicated that earlier outpatient paracentesis may reduce the progression of OHSS and prevent hospitalisation in women.

**Methods and analysis:**

This UK, multicentre, pragmatic, two-arm, parallel-group, adaptive (group sequential with one interim analysis), open-label, superiority, confirmatory, group sequential, individually randomised controlled trial, with internal pilot will assess the clinical and cost-effectiveness and safety of outpatient paracentesis versus conservative management (usual care) for moderate or severe OHSS. 224 women from 20 National Health Service and private fertility units will be randomised (1:1) and followed up for up to 13.5 months. The primary outcome is the rate of OHSS related hospital admission of at least 24 hours within 28 days postrandomisation. The primary analysis will be an intention to treat with difference in hospitalisation rates as measure of treatment effect. Secondary outcomes include time to resolution of symptoms, patient satisfaction, adverse events and cost-effectiveness. A qualitative substudy will facilitate the feasibility of recruitment. Participant recruitment commenced in June 2022.

**Ethics and dissemination:**

London—Southeast Research Ethics Committee approved the protocol (reference: 22/LO/0015). Findings will be submitted to peer-reviewed journals and abstracts to relevant national and international conferences, as well as being disseminated to trial participants and patient groups.

**Trial registration number:**

ISRCTN71978064.

STRENGTHS AND LIMITATIONS OF THIS STUDYThis is the largest randomised controlled trial to date which aims to establish whether outpatient paracentesis reduces the rate of ovarian hyperstimulation syndrome (OHSS)-related hospital admissions in those presenting with moderate or severe OHSS, compared with usual care.Due to the nature of the intervention, it is not possible to blind study participants or clinicians.Measures are taken to reduce the impact of this, including a secondary independent blinded adjudication of hospital admissions and blinding of trial statisticians.Patients with lived experience were involved in the design of the trial and will provide advice throughout delivery.

## Introduction

Ovarian hyperstimulation syndrome (OHSS) is the most significant short-term complications of pharmacological ovarian stimulation for assisted conception. It is most often seen in women with a high ovarian reserve, who are prone to an excessive response to gonadotropin stimulation.

There is no universally accepted classification of OHSS. In the UK, the Royal College of Obstetricians and Gynaecologists (RCOG) classification is widely used and includes mild, moderate, severe or critical categories.^1^ Moderate cases involve the build-up of fluid in the abdomen (called ascites), increased ovarian size, and abdominal distention and discomfort. In severe cases, fluid retention and dehydration can lead to changes to the constitution of the blood (haemoconcentration and hypoalbuminaemia); critical cases can lead to respiratory distress, thrombosis, disturbed renal and liver functions, and rarely death.^2^

OHSS can be further classified into early and late (table 1). Early OHSS is usually caused by the ovarian stimulation drugs given during treatment and usually occurs within 7 days after the final drug Human chorionic gonadotropin (hCG) is given. Late OHSS usually occurs 10 days or more after the administration of hCG and is caused by endogenous hCG of the resulting pregnancy. The late type is usually more difficult to control, runs a longer course and is more severe.^3^

**Table 1 T1:** Categorisation of OHSS and its severity, based on the RCOG definitions^1^

**Categorisation of OHSS**	
Early OHSS	Caused by the ovarian stimulation drugs given during assisted reproductive technologies and occurs usually up to 7 days of the final trigger drug (hCG) being given.
Late OHSS	Usually occurs 10 or more days after the trigger drug is given.
Where a patient presents at day 8 or 9 clinical judgement will be used to classify the early or late OHSS.	
**Severity of OHSS**	
Mild OHSS	Abdominal bloating Mild abdominal pain Ovarian size is usually below 8 cm
Moderate OHSS	Patients do not meet the criteria of severe (described below) and have fluid accumulation in abdomen (ascites), confirmed by ultrasound scan. The following symptoms may also be present: Moderate abdominal pain Increased ovarian size of usually 8–12 cm Nausea with or without vomiting Some degree of clinical judgement may be needed to confirm the diagnosis of moderate OHSS.
Severe OHSS	Patients have fluid accumulation in abdomen (clinical ascites/clinically detectable fluids), confirmed by ultrasound, with or without hydrothorax The main distinguishing features are any of the following: Low urine output (oliguria) (<300 mL/day or <30 mL/hour) Haematocrit>0.45, (confirmed via full blood count (FBC) test) Ovarian size>12 cm.
Critical OHSS	Clinically obvious ascites, with one of the following features: the patient has a tense ascites or a large hydrothorax Haematocrit level >0.55 (confirmed via FBC test)* A white cell count of over 25 000 /mL (confirmed via FBC test) Anuria (very little/no urine) (<100 mL/day) Thromboembolism Acute respiratory distress syndrome

*Haematocrit level is the most important measurement.

hCG, human chorionic gonadotropin; OHSS, ovarian hyperstimulation syndrome; RCOG, Royal College of Obstetricians and Gynaecologists.

Clinical practice usually involves monitoring the patient until the condition becomes severe, when the patient is admitted to hospital, as recommended by the RCOG guideline.^1^ Inpatient management often includes drainage of ascitic fluid (paracentesis) which can result in a significant improvement of the condition and in renal blood fluid, urine output and reversal of the haematological abnormalities.^4–6^ Complications such as venous thromboembolism can have long-term health problems lasting well beyond the length of the pregnancy.

Although mild forms are fairly common (approximately one in three women undergoing IVF (in vitro fertilisation) treatment), more severe OHSS (up to 8% for combined moderate and severe OHSS)^1^ can have a significant impact on a woman’s health resulting in prolonged hospitalisation and posing a significant economic burden on both patient and National Health Service (NHS). With over 69 000 IVF cycles performed in the UK in 2019 alone,^7^ the burden of the problem becomes evident.^1^ It is, therefore, important to look into novel approaches to improve outcomes and the management of complications associated with IVF.^8^

Small retrospective studies^9 10^ and a larger uncontrolled study^11^ have suggested that transvaginal paracentesis can reduce the need for hospitalisation to between 2.9% and 14% of patients. Another small cohort study identified patients with moderate OHSS at risk of this progressing to severe OHSS and reduced this progression with only 1–3 paracentesis procedures.^12^ There is also some evidence to suggest transabdominal administration of paracentesis can prevent inpatient hospitalisation compared with those managed supportively.^13^ Furthermore, preliminary studies have safely and effectively managed patients in the outpatient setting by using a pigtail catheter to drain ascetic fluid.^14 15^ All of these studies have still achieved high pregnancy rates of 68%^13^ and 100%.^12^ Modelling also suggests that it would be more cost-effective to treat patients with moderate or severe OHSS with early outpatient paracentesis (OP), compared with less active management and inpatient admission.^16^

Preliminary results have been encouraging and suggest promising safety and effectiveness of OP.^9–13 15 17^ However, this needs to be evaluated in a robust and adequately powered randomised controlled trial (RCT) taking into consideration variabilities in practice across fertility units.

This study aims to establish the clinical and cost-effectiveness, safety and acceptability of OP as an active management for women with moderate or severe OHSS. The primary objective is to establish whether OP reduces the rate of OHSS related hospital admissions in those presenting with moderate or severe OHSS compared with usual care (UC). Secondary objectives are to:

Establish whether OP prevents the escalation of OHSS severity.Establish whether OP reduces the time taken for OHSS symptoms to resolve.Establish the safety of OP as an active intervention for moderate or severe OHSS.Explore whether OP would improve patient satisfaction and quality of life.Establish whether OP is cost-effective by examining healthcare resource use and patient costs.Facilitate the feasibility of conducting the RCT by identifying problems with the conduct of the RCT during an internal pilot.

Pretrial development work involved qualitative interviews with clinicians and patients exploring the feasibility and acceptability of earlier active management protocols. These results fed into a consensus event to confirm the treatment protocol used in the RCT. We also undertook a comprehensive audit of proposed RCT centres to inform the parameters used to design the RCT.

## Method and analysis

Full detailed methods of the STOP OHSS trial are included in the trial protocol, available via the trial registry (https://www.isrctn.com/ISRCTN71978064).

STOP-OHSS is a pragmatic, parallel open-label, multicentre, superiority, adaptive, group sequential, confirmatory RCT with an internal pilot (after 15 of 31 months recruitment) to assess feasibility aspects (figure 1). Eligible participants will be individually randomised (1:1) to receive either routine treatment or OP plus daily diary monitoring.

**Figure 1 F1:**
[figure not shown]
Study flow diagram. CSQ-8, Client Satisfaction Questionnaire 8; FBC, full blood count; OHSS, ovarian hyperstimulation syndrome.

The trial is a collaboration between The Jessop Wing, Sheffield Teaching Hospital NHS Foundation Trust and the University of Sheffield—Clinical Trials Research Unit (CTRU) who are responsible for the conduct of the trial. It is funded by the National Institute of Health and Care Research Health Technology Assessment, who had no involvement in the study design or conduct; or the decision to submit the protocol for publication. The trial will be conducted in compliance with the protocol, Good Clinical Practice and regulatory requirements. Substantial protocol amendments will be communicated to all relevant bodies. Main trial recruitment commenced June 2022 and is ongoing.

### Internal pilot

An internal pilot will use the same procedures as the main trial and will assess the following after 15 months of a planned 31-month recruitment period:

Participant recruitment (both arms).Retention of randomised participants (both arms).Delivery of the OP treatment (only OP arm).

At the end of the pilot phase, the trial steering committee (TSC) will report to the funder on whether criteria have been met to continue.

### Recruitment

The trial will recruit women attending approximately 20 NHS or private UK Fertility Units, undergoing assisted reproductive technologies (including IVF, intracytoplasmic sperm injection and intrauterine insemination) and who experience moderate or severe, early or late OHSS symptoms. Participation is voluntary and choosing not to participate will not negatively influence the woman’s treatment. Consent can be withdrawn at any stage. Women will be identified by the following recruitment strategies.

Monitoring cases—women who are considered at risk of developing moderate or severe OHSS due to various risk factors such as a previous episode of OHSS, high response to stimulation with increased follicular activity, >15 eggs with or without symptoms of OHSS, polycystic ovary syndrome, high levels of anti-Müllerian hormone (greater than 30 pmol/L, younger women (<30 years) who have a good ovarian reserve and are, therefore, known to respond well to treatment, low body mass index or any symptoms of OHSS such as bloating and nausea. Incident cases—women with moderate or severe OHSS who were not previously identified as at risk.

Potentially eligible participants will be approached as soon as possible after the diagnosis of moderate or severe OHSS and, where possible, initial eligibility screening has taken place. Women may also be alerted to the trial via the trial website or posters displayed at the fertility unit.

Research staff will provide the patient with the participant information sheet and/or link to a trial animation video outlining the study as soon as they become aware the woman is potentially eligible. Prior to randomisation, full written informed consent (see online supplemental file 1) will be obtained by a suitably trained clinician researcher at the clinic visit. Standard consent includes a provision for anonymised data to be shared with other researchers. Baseline data will be collected at this visit and participants will be randomised.

10.1136/bmjopen-2023-076434.supp1Supplementary data

Women will be considered suitable if they meet the following eligibility criteria.

Inclusion criteria:

Women presenting with moderate or severe, early or late OHSS.Patients able and willing to attend weekly follow-up appointments in person or remotely, daily remote appointments/phone calls and able to undertake self-monitoring at home.

Exclusion criteria:

OHSS-related exclusion criteria:Significant pain or vomiting requiring hospitalisation.Pulmonary embolism.When in the judgement of the clinician, the patient’s condition is severe enough to warrant admission to a high-dependency care unit (such as critical OHSS as defined in the RCOG green-top guidelines), and therefore, not suitable for outpatient management.Non-OHSS-related medical conditions: a concurrent medical condition requiring immediate inpatient management.Patients who have been previously randomised but later present with moderate or severe OHSS symptoms in subsequent cycles after their initial trial involvement.Participation in other trials involving ovarian stimulation or ovarian response.

### Centralised research nursing delivery team

Local research teams will be supported in recruiting participants and ongoing management of the trial protocol procedures from the central research nursing delivery team based at the Jessop Wing, Sheffield Teaching Hospitals NHS Foundation Trust. This team will support local discussions with potential participants about trial participation, randomisation procedures and monitoring and routine follow-up visits in both trial arms.

### Randomisation and concealment

Patients will be randomised using a centralised web-based system (SCRAM) hosted by Sheffield CTRU, which has user-restricted functionalities granting access rights to specific areas as appropriate. The sequence will be computer generated using permuted block randomisation stratified by recruiting site and severity of OHSS. Block sizes will be disclosed during dissemination of findings and only the randomisation (trial) statistician(s) not involved in the recruitment process will know the block sizes during the trial. The trial statistician will generate the randomisation sequence; however, they will not have access to the generated sequence. Research staff at recruiting centres will use a web-based computer system with restricted access rights to enter participant details; randomisation outcome will then be revealed. Re-randomisation will not be permitted.

### Intervention and control

Following randomisation, women in the intervention arm will have OP performed in the outpatient setting as soon as clinically possible. Sites will follow their own local procedures for conducting paracentesis either abdominally or vaginally by a suitably trained doctor, advanced nurse practitioner or radiologist in the fertility, gynaecology or radiology unit and while the trial does not dictate how to perform the intervention, guidance will be offered.

If rehydration is required via intravenous methods, this will be at the discretion of the attending clinician. If a large volume of fluid is removed, then intravenous colloid therapy should be considered. If this administration of fluid results in overnight inpatient hospitalisation it will not be viewed as meeting the trials primary outcome relating to hospitalisation. Some patients may require multiple drainage which can be performed if the participant has a reaccumulation of ascites.

Women in the UC group will not have the paracentesis performed in an OP setting and will be monitored by their clinical team as per UC. If UC at the site involves administering paracentesis on an outpatient basis for treatment of OHSS then the site will be requested to stop routinely providing this for participants in the UC arm.

Both groups of women will be provided with access to a diary (either in paper format or sent electronically using Research Electronic Data Capture (REDCap)^18^ hosted at The University of Sheffield for the purpose of daily self-report of weight, abdominal girth, diarrhoea, vomiting, pain, shortness of breath, fluid input and urine output. This information will be used by the clinical team in the intervention arm on a daily basis to inform further management and whether to perform further OP. The UC group will also perform daily self-monitoring, but these data will be sent directly to CTRU for input into the database and will not be available to be reviewed by site staff.

Some fertility units undertake other preventative measures (eg, dopamine agonists, gonadotropin-releasing hormone (GnRH) antagonists, cessation of IVF cycle) to reduce the risk of OHSS and details of these measures will be collected during the trial, along with information on the provision of care within the conservative management arm. Rarely, patients may be prescribed GnRH antagonists as treatment for established moderate or severe OHSS. This will not be prohibited for trial participants in both arms and data will be collected on GnRH use within the trial.

Participants may wish to stop study treatment, or there may be a clinical need to stop treatment. Participants randomised to the intervention arm, who withdraw from receiving the intervention will continue to be followed-up and will remain in the trial, unless they request to be withdrawn.

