OHSS-related hospitalisation for at least 24 hours within 28 days of randomisation.

Secondary outcomes:

Need for OHSS-related hospitalisation within 28 days—independent blinded central assessment.Time to resolution of OHSS assessed within 28 days of randomisation.Progression of OHSS severity within 28 days of randomisation.Cumulative length of OHSS-related hospitalisation.Live birth, pregnancy outcomes, neonatal death and serious adverse events (SAEs) including congenital abnormalities in the new-born within 13.5 months of randomisation.The occurrence of thrombosis, embolism and significant infections requiring antibiotic treatment or hospitalisation within 90 days of randomisation.AEs within 28 days of randomisation.Patient satisfaction assessed using the Client Satisfaction Questionnaire 8^19^ based on total scores at 28 days postrandomisation.EQ-5D-5L participant quality of life daily and at 28 days postrandomisation.Health resource use and patient costs at 28 days postrandomisation.

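### The exemption for overnight stays after intravenous fluid conflicts with the 24-hour primary outcome and, if it reaches stays of 24 hours or more, would remove events mainly from the outpatient paracentesis arm

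*Protocol article*

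**What the plan says.** The primary outcome in the Outcomes section of the protocol article is any "OHSS-related hospitalisation for at least 24 hours within 28 days of randomisation". No type of admission is excepted.

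The Intervention and control section adds a condition. It first leaves intravenous rehydration to the attending clinician, then says "If a large volume of fluid is removed, then intravenous colloid therapy should be considered", and continues: "If this administration of fluid results in overnight inpatient hospitalisation it will not be viewed as meeting the trials primary outcome relating to hospitalisation". No length of stay is given beyond the word overnight, and no arm is named.

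The same section describes who is drained as an outpatient. In the intervention arm, "women in the intervention arm will have OP performed in the outpatient setting as soon as clinically possible". For the control arm, "Women in the UC group will not have the paracentesis performed in an OP setting". Where a site's usual care includes outpatient drainage, "the site will be requested to stop routinely providing this for participants in the UC arm".

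Under Statistical analysis, the primary effect measure is the absolute difference in hospitalisation rates, and the unadjusted difference drives the interim futility decision. Under Blinding, a blinded adjudicated version of the outcome is planned as an additional analysis.

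**The concern.** The two sections do not give the same endpoint. A woman who stays 30 hours for OHSS, where the stay resulted from intravenous fluid, is an event under Outcomes and a non-event under Intervention and control.

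The difference need not fall evenly on the arms. The exemption follows the sentence on colloid after large-volume removal, and outpatient drainage is planned for all OP women and for no UC women. In UC, drainage would usually take place during an inpatient stay, which already counts if it lasts 24 hours. Admissions that follow the intervention itself could then be scored as admissions avoided.

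Three results would be affected: the primary risk difference, the futility decision, which uses the same observed difference, and possibly the cost per hospitalisation avoided, if the health economic analysis uses the same count.

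**Working it through.** **Step 1. What the exemption can change.** Sort stays that result from fluid by length.
- Under 24 hours: not an event under Outcomes and not an event under the exemption. Nothing changes.
- 24 hours or more: an event under Outcomes, a non-event under the exemption as worded.

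So the sentence either has no effect or removes events of 24 hours or more. The text does not say which is meant.

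**Step 2. Inputs, from Sample size and interim analyses.** UC rate 41%; target reduction 20 points (41% against 21%); one-sided 2.5%; 73 per arm at the interim and 112 per arm at the end; stop for futility if the observed reduction is below 4.5 points.

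**Step 3. Reproduce the plan's figures.** The calculation is an exact two-binomial enumeration. At the interim 0.045 × 73 = 3.285, so the trial continues only if UC has at least 4 more events than OP. The final test rejects if the pooled z is at least 1.96.
- Equal rates (41% and 41%): futility stop 72.2% (the plan states 72.2%); one-sided error 2.4%.
- 41% against 21%: power 90% (the plan states 90%); futility stop 2.1% exactly, or 1.9% by normal approximation (the plan states 1.9%).

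The pooled-variance formula gives 111 per arm against the planned 112. The sample size is sound; the question concerns the endpoint alone.

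**Step 4. Effect of uncounted stays.** Let x be the percentage points of OP women with an OHSS-related stay of at least 24 hours that is not counted. The article gives no value, so x is an assumption. With 41% truly admitted in both arms, the counted OP rate is 41% − x and the apparent benefit is x.

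| x (points) | Counted OP rate | One-sided error | Correct futility stop |
|---|---|---|---|
| 0 | 41% | 2.4% | 72% |
| 1 | 40% | 3.4% | 68% |
| 2 | 39% | 4.7% | 63% |
| 5 | 36% | 11.3% | 49% |

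An x of 5 points would by itself exceed the 4.5-point futility threshold and lie inside the 4.7 to 5.7 point range that the article gives for cost saving.

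**Step 5. Is imbalance the cause?** With 5 points uncounted in OP and 2.5 in UC, the error is 5.7% (normal approximation). With 5 points uncounted in both arms it returns to about 2.5%. The distortion comes from unequal removal.

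**The case against.** The strongest reply is that the exemption only restates the 24-hour rule. Overnight ordinarily suggests one night, which is often shorter than 24 hours, and the sentence may simply tell sites that such a stay is not an event. On that reading there is no bias, only loose wording. The reading is reasonable and cannot be excluded. But the sentence gives no number of hours, and a one-night stay can pass 24 hours, so the text does not secure it either.

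A reader might infer more than the article supports in four respects.
- *That the exemption applies to OP alone.* The rule names no arm, and its link to discretionary rehydration could extend to UC women. Sites are only asked to stop routine outpatient drainage in UC, so occasional use is possible. What remains is that removal would fall mainly in OP, by placement and by design.
- *That unblinded staff decide which stays are exempt.* Clinicians are unblinded, but the article does not say who makes this decision.
- *That a large error inflation is established.* Exempting a fifth of OP admissions would give a 24% one-sided error, but nothing in the article supports that share. The true share could be near zero.
- *That nothing guards against the problem.* A blinded adjudicated outcome is prespecified, and reasons for admission and cumulative stay are collected. These help, but adjudication is an additional analysis, its handling of fluid-related stays is not described, and it governs neither the primary result nor the interim decision.

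The article is also condensed, and the full protocol may settle the point. Still, the article itself states both rules, and they disagree.

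**Conclusion.** The point holds as an inconsistency in the primary endpoint with a conditional bias. As written, a stay of 24 hours or more that results from intravenous fluid is an event in one section and not in the other. If such stays are removed, they would come mainly from OP and favour OP.

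The size cannot be stated from the documents. The figures for 1, 2 and 5 points assume equal true rates of 41%, removal in OP only, and values of x chosen for illustration. The error inflation requires that such stays occur and are removed unequally; it disappears if the exemption is confined to stays under 24 hours. The article does not show that the endpoint is in fact counted differently by arm.

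The passages should be reconciled before the outcome is used for the interim or final analysis, because the primary estimate and the stopping rule both rest on it.

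**What to change.** Reconcile the two sections so that every OHSS-related stay of at least 24 hours within 28 days counts in both arms, whatever treatment was given during it. State that the sentence on fluid covers only stays under 24 hours.

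If the exempted version is wanted, report it as a sensitivity analysis, with the same exemption applied to both arms by the blinded adjudicators.

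The cost is one sentence in the outcome definition and in site guidance. Reasons for hospitalisation are already collected (Table 2).

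The downside is that the observed OP effect may be slightly less favourable. If the planning rate of 21% already left such stays out, which the article does not say, counting them would also reduce power. With 2 or 5 further points in OP the true reduction would be 20 − 2 = 18 or 20 − 5 = 15 points, and power at 112 per arm would be about 82% or 66%. If 21% already describes all stays of at least 24 hours, the sample size stands.
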